## Set-up of course of therapy

In accordance with the technical guideline on the drug clinical trial for treatment of major depressive disorder (exposure draft) (2013), 6-8 weeks is recommended as the course of therapy for acute phase of major depressive disorder, thus the course of therapy is set as 6 weeks in this study.

## Sample size calculation

This is one phase 2 dose-exploratory study, according to the requirements of CFDA drug regulatory regulationsat, at least 200 valid cases need to be completed, and considering a (20-30)% fall-off rate, a total of 260 cases are expected to be enrolled in consideration of the possible drop-out rate of 30% during the study, and 1:1:1:1:1 randomized to Ansofaxine Hydrochloride Extended Release Tablet 40, 80, 120 and 160 mg dose groups or placebo group, there will be at least 52 screening eligible cases in each group.

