| --- | --- |
| **Investigational product** | Ansofaxine Hydrochloride Sustained-release Tablets |
| **Trial title:** | A Multicenter, Randomized, Double-Blind, Placebo-controlled, Dose-finding Clinical Trial to Preliminarily Evaluate the Efficacy and Safety of Ansufaxine Extended-release Tablets for the Treatment of Major Depressive Disorder (MDD) |
| **Objectives** | Primary objective:  To find the optimal dose of Ansufaxine extended-release tablets in the treatment of MDD.  Secondary objective:  To evaluate the preliminary efficacy and safety of Ansufaxine extended-release tablets for the treatment of MDD, thereby providing a basis for the determination of study design and dosing regimen for a phase 2I clinical trial. |
| **Subject Population** | Patients aged 18~65 years who meet DSM-IV-TR diagnostic criteria for major depressive disorder |
| **Number of subjects** | 5 groups, 52 subjects/group, a total of 260 subjects |
| **Study Methods** | Multicenter, randomized, double-blind, placebo parallel controlled, dose exploratory |
| **Investigational product** | 1. Study drug: Ansofaxine Hydrochloride Extended Release Tablet, specification 40mg, researched, developed and provided by Shandong Luye Pharmaceutical Co., Ltd. 2. Control drug: Simulator for Ansofaxine Hydrochloride Extended-release Tablet (placebo), researched, developed and provided by Shandong Luye Pharmaceutical Co., Ltd. |
| **Group and**  **Dosage and administration** | 1. Trial Grouping:   260 patients with major depressive disorder who meet the enrollment criteria will be randomized to 4 study drug dose groups of and 1 placebo group, i.e., 52 patients each group.   1. Dosage and administration:   Wash-out period: placebo two tablets, once per day, administered under fasted state or after meal at a relatively fixed time in the morning, for consecutive one week.  Treatment period: Ansofaxine Hydrochloride Extended Release Tablet 40mg, 80mg, 120mg, 160mg or placebo orally, once per day, administered under fasted state or after meal at a relatively fixed time in the morning, for consecutive 6 weeks. |
| **Course of therapy** | A total of 8 weeks, including a screening/wash-out period of two weeks and treatment period of 6 weeks. |
| **Visit frequency** | Follow-up at screening, baseline (Day 0), 1, 2, 4 and 6 weeks after administration. |

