# Trial design

## Test method

This study was a multicenter, randomized, double-blind, placebo parallel-controlled, dose-finding phase 2 clinical trial to find the optimal dose of LY03005 extended-release tablets for the treatment of MDD and to evaluate the preliminary efficacy and safety, providing a basis for the design of phase 2I clinical trials and the determination of dosing regimens.

This study consisted of two periods: a screening and washout period of up to 2 weeks (8 days recommended) and a double-blind treatment period of 6 weeks. The screening and washout period were expected to last from 8 days (recommended) to 2 weeks. After screening, eligible patients with MDD entered a 1-week placebo washout period, during which they took 2 placebo tablets orally once a day in the morning for 7 consecutive days. 260 patients with MDD who still met the inclusion criteria after the placebo washout then entered a double-blind treatment period of 6 weeks. They were randomly assigned to placebo or one of four fixed does LY03005 extended-release tablets (40, 80, 120 or160mg/day) using a 1:1:1:1:1 randomization schedule. Subjects took 4 tablets of test drug or placebo once a day and returned for follow-up visits at the weekends of study week 1, 2, 4 and 6.

Efficacy endpoints included 17-item Hamilton Depression Scale (HAM-D17), Hamilton Anxiety Rating Scale (HAM-A), Clinical Global Impression (CGI) and Visual Analog Scale for Pain Intensity (VAS-PI). Safety evaluation included adverse events, vital signs, physical examination, laboratory tests (hematology, urinalysis, blood chemistry test and serological test), and 12-lead ECG.

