### Analysis set of clinical trial

The analysis set defined for this study is as below:

1. Full analysis set (FAS)

It includes all the randomized subjects who were administrated at least 1 dose of double-blind study drug and had primary efficacy evaluation at baseline and at least one primary efficacy evaluation after the first dose of double-blind treatment. Unless otherwise specified, LOCF (last observation carried forward) will be used for the missing value imputation in the FAS.

FAS is the primary analysis data set for this trial.

1. Per protocol set (PPS)

It includes all the subjects who completed visit 6 and have no major protocol deviation.

1. Safety set (SS)

It includes all the subjects who were randomized and administrated at least one dose of the double-blind study drug. Subjects who were dispensed study drug but did not administrate any study drug will not included in SS.

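### At the 30% drop-out used to justify it, a total of 260 patients gives 182 completed cases, not the 200 that Section 4.6 requires

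*Protocol*

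**What the plan says.** Section 4.6 (Sample size calculation) gives no effect size, standard deviation or power. Its basis is a requirement, attributed to drug regulations, that "at least 200 valid cases need to be completed". It allows for losses twice in the same sentence: first as a range, "considering a (20-30)% fall-off rate", and then as the single rate tied to the total, "a total of 260 cases are expected to be enrolled in consideration of the possible drop-out rate of 30% during the study".

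The Abstract (Number of subjects) repeats the total as "5 groups, 52 subjects/group, a total of 260 subjects".

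Section 4.1 (Test method) fixes the point at which the 260 are counted: "260 patients with MDD who still met the inclusion criteria after the placebo washout then entered a double-blind treatment period of 6 weeks". Those patients are then allocated "using a 1:1:1:1:1 randomization schedule".

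Section 11.2 (Analysis set of clinical trial) makes the full analysis set primary, with LOCF for missing values. It defines the per-protocol set by completion: "It includes all the subjects who completed visit 6 and have no major protocol deviation".

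**The concern.** The target, the drop-out rate and the total all stand in one sentence, and the third does not follow from the first two. Losing 30% of 260 leaves fewer than 200.

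This matters because the 200 completed cases are the only stated reason for the size of the trial. With no power calculation behind it, an error here leaves the total without the support the protocol claims for it. The protocol also presents 200 as a minimum set by regulation, so under its own assumption it plans to miss a figure it says it must reach.

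**Working it through.** **Inputs, all from the protocol**

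- Target: 200 completed valid cases (Section 4.6).
- Drop-out: 30% in the clause that sets the total; 20–30% earlier in the same sentence (Section 4.6).
- Planned total: 260, as five groups of 52 (Abstract; Section 4.6).
- Counting point: entry to double-blind treatment, after the placebo wash-out (Section 4.1). The 260 is therefore not a screening number, and no reserve stands behind it.

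**Reproducing the stated total**

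- Adding the drop-out percentage to the target: 200 × (1 + 0.30) = 260. Per group, 200/5 = 40 and 40 × 1.30 = 52.
- Dividing the target by the proportion retained: 200 / (1 − 0.30) = 285.7, rounded up to 286.

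The first formula returns both stated figures exactly. The second does not. The protocol does not show its working, so the route to 260 is an inference, but the match on the total and on the group size makes it the likely one. The first formula is wrong because drop-out applies to the number enrolled, not to the number wanted at the end.

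**Forward check: completed cases = 260 × (1 − d)**

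| Drop-out d | Completed cases | Per group | Against 200 |
| --- | --- | --- | --- |
| 20% | 208 | 41.6 | +8 |
| 25% | 195 | 39.0 | −5 |
| 30% | 182 | 36.4 | −18 |

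The shortfall at 30% is 18/200 = 9%.

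**Break-even**

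1 − 200/260 = 23.1%. Within the stated 20–30% range, 260 falls short for every rate above that, which is (30 − 23.1)/(30 − 20) = 69% of the width of the range.

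**Chance of reaching 200**

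Assume that patients drop out independently at a common rate, so that the number of completers is binomial with n = 260. The probability of at least 200 completers is then about 90% at 20% drop-out, 26% at 25% and 0.8% at 30%.

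**Enrolment that would hold 200 at 30%**

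- In total: 286, since 286 × 0.70 = 200.2.
- With five equal groups: 40/0.70 = 57.1, rounded up to 58, and 58 × 5 = 290. This gives 290 × 0.70 = 203 expected completers.

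**The case against.** Four points can be made for leaving the text alone.

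1. **30% is the top of a range and is called only possible.** At 20%, the 260 yields 208, and the target holds up to 23.1%. This is true, and 182 should be read as the unfavourable end of the stated range. But the clause that sets 260 names 30% as the loss it allows for, and the total already fails at the midpoint of the range (195).

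2. **The primary analysis is not sized by completers.** The full analysis set needs one dose, a baseline score and one post-baseline HAM-D17 score, and LOCF fills in the rest. A patient who leaves after the Week 1 visit can still count. This stands, and it limits the consequence: 182 is not the expected number in the primary analysis. It does not rescue Section 4.6, whose target is cases to be completed. A drop-out allowance has a purpose only if drop-outs do not count towards that target.

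3. **No operating characteristic changes.** The trial is exploratory, with a type I error of 0.1, no multiplicity adjustment and no stated power. This also stands. It means the error is confined to the stated basis for the size, but that is the only basis given.

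4. **The regulation is not available here.** Whether it counts completers, evaluable patients or exposed patients cannot be checked, and the protocol does not define a valid case. What is shown is therefore an internal inconsistency. It is not evidence of non-compliance with a regulation.

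**Conclusion.** The point holds. Section 4.6 is wrong as written: its total does not deliver its target at the drop-out rate it cites. The expected shortfall at 30% is 18 completed cases (182 against 200, or 36.4 against 40 per group), and the total supports the target only up to 23.1% drop-out.

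The conclusion rests on two readings. A valid case is taken to be a patient who completes treatment, which follows the section's own wording. The 260 is taken as the number randomised, which Section 4.1 states. The effect is limited to completers, the per-protocol set (which also loses major deviators) and the observed-case analyses.

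**What to change.** Restate Section 4.6 so that the three figures agree, for example:

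> 260 patients will be randomised (52 per group). This gives 200 completed valid cases if drop-out does not exceed 23%. At 30% drop-out, about 182 completed cases (about 36 per group) are expected.

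Remove the claim that 260 allows for 30% drop-out, and say in one clause what counts as a valid case. This costs a sentence or two of text and a slightly less favourable stated figure. It needs no extra patients.

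The restatement is enough only if the sponsor accepts fewer than 200 at the upper end of its range. If 200 must hold at 30%, enrolment has to rise to 286, or to 290 with five equal groups. That is 26 or 30 more patients, and the Abstract, Section 4.1 and Section 4.6 would have to change together. The sponsor should state which of the two applies.

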## Randomization method

MagMin minimized dynamic randomization system (<http://rct.fmmukq.com>) is used for dynamic randomization. The randomized algorithm is Pocock & Simon. After verifying that the patient is eligible per inclusion criteria and exclusion criteria, the Investigator will log in the MagMin randomization system using the account and password and get the assignment of unique randomization number and drug number for the patient. Eligible patients will be randomized 1:1:1:1:1 to receive LY03005 40mg/day, 80mg/day, 120mg/day, 160mg/day or placebo, respectively. The baseline HAM-D_17_, gender and age score will be used as important prognostic factors for baseline balancing across groups. Within each randomization, patients will be stratified for:

- HAM-D17 total score at baseline (20-30, 31-40, ≥41)
- Gender (Male, Female)
- Age, years (18-30, 31-40, 41-50, 51-65)

## Requirement and method for blinding

Double-blind, single-dummy technique is used. The drug randomization listsare generated by the independent 3rd party using SAS code. A randomized block schedule will be used for the drug randomization lists. The study drug will be manufactured, packaged and provided by Shandong Luye Pharma Co., Ltd., and then will be coded uniformly by the independent 3rd party per the drug randomization lists. In accordance with the drug number replied from MagMin randomization system, subjects will be given the corresponding drugs. Any drug use method that violates this rule will be regarded as violation. Drug number will remain unchanged throughout the study. Each patient will be provided by investigators with the study drug of the same number in divided doses.

# Selection of Subjects

## Inclusion criteria

1. Male and female outpatients or inpatients aged 18~65 years;
2. Subjects who meet the Diagnostic and Statistical Manual of Mental Disorders, Fourth Edition (DSM-IV-TR) criteria for MDD with a single or recurrent episode(296.2/296.3), without psychotic features;
3. Subjects who have 17-item Hamilton Depression Scale (HAM-D_17_) total score≥20 points at the screening and baseline visit;
4. Subjects who have Depressed Mood of Hamilton Depression Scale (HAM-D_17_) ≥2 points at the screening and baseline visit;
5. Subjects who have clinical Global Impression-Severity Scale (CGI-S) score ≥4 points at the screening and baseline visit;
6. Women of childbearing age (e.g., women who have not experienced sterilization or have had menopause for less than 1 year) who have negative result shown by the urine pregnancy test at the screening and baseline visit; male and female subjects of childbearing age who agree to use a medically acceptable form of contraception for the duration of the study and until at least 28 days after the last oral dose of the study medication;
7. Subjects who voluntarily participate in the trial and sign informed consent forms and who are able to comply with the procedures for scheduled visits, treatments, laboratory tests and other research procedures.

## Exclusion criteria

1. Subjects who are allergic or known to be allergic to venlafaxine and desvenlafaxine
2. Subjects who have previously failed treatment with venlafaxine at an adequate dose for an adequate time, or patients who have refractory depression and have previously failed treatment with at least 2 types of antidepressants at an adequate dose for an adequate time;
3. Subjects who have greater than 25% change in HAM-D17 total score at baseline from screening visit;
4. Subjects who have clear suicide attempt or behavior with Suicide score in HAM-D17 ≥ 3 points;
5. Pregnant or breastfeeding women, or men and women of childbearing age who do not use a medically acceptable form of contraception or fail to continue contraception until 28 days after the last dose of the study medication;
6. Subjects with DSM-IV-TR axis I diagnoses other than MDD, who receive treatment for such diagnoses (including current or previous diagnoses of anorexia nervosa or bulimia nervosa), or who have been diagnosed with depressive neurosis within the past 2 years; Depressive episode secondary to other psychiatric disorder or somatic disease;
7. Subjects with MDD secondary to other organic or mental disorders;
8. Subjects with a history of seizures (except spasms caused by infantile hyperpyretic convulsions);
9. Subjects who have received electroconvulsive therapy (ECT) within 3 months prior to screening or need current ECT treatment per investigator’s judgment, have received systematic psychotherapy (interpersonal relationship therapy, dynamic therapy, cognitive behavioral therapy) within 3 months of screening, have received transcranial magnetic stimulation (TMS) 3 months prior to screening, or have received light therapy 2 weeks prior to screening;
10. Subjects who have regularly taken anti-depressants within 2 weeks prior to screening, or have withdrawn from psychotropic drugs for less than 7 half-lives (at least 2 weeks for monoamine oxidase inhibitors and at least 1 month for fluoxetine) before randomization/enrollment;
11. Subjects with a history of serious unstable cardiovascular, hepatic, renal, blood or endocrine diseases;
12. Subjects with hypertension whose blood pressure is poorly controlled (SBP≥140 mmHg or DBP≥90 mmHg at the screening and baseline visit);
13. Subjects with a history of gastrointestinal diseases known to interfere with drug absorption or excretion, or those with a history of surgery that is known to interfere with drug absorption or excretion;
14. Subjects with a history of increased intraocular pressure or narrow angle glaucoma;
15. Subjects with clinically significant abnormal results as considered by the investigator shown by a physical examination, laboratory test or urine drug test (e.g., ALT or AST> 1.5 times the upper limit of normal; Creatinine clearance > the upper limit of normal; abnormal measurements of thyroid function which are of clinical significance);
16. Subjects with Electrocardiogram (ECG) abnormalities that are clinically significant at screening and baseline, and investigators believe that it is inappropriate for the subjects to be enrolled, such as QTc interval >450 ms for male and QTc interval >460 ms for female;
17. Subjects who have participated in clinical trials on other drugs within 3 months prior to screening;
18. Subjects with serious acute or chronic diseases, mental illnesses or clinically significant abnormalities as shown in laboratory tests, of which investigators believe that the subjects are not suitable for this study

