## Elimination criteria

For those subjects enrolled into this clinical study, they were removed from this trial if one of the following criteria is met:

(1) Subjects who did not meet the inclusion criteria or met the exclusion criteria;

(2) Subjects who did not have any medication records;

(3) Subjects with no records of efficacy and safety information after the baseline.

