## Baseline

**Visit 2 — — Day 0**

- Enquiry about the occurrence of adverse event;
- Enquiry about concomitant medications;
- Evaluation: HAM-D_17_、HAMA、CGI-S、VAS-PI；
- Vital signs: blood pressure and pulse rate (in supine and orthostatic position), temperature, respiratory frequency;
- Weight;
- 12-Lead ECG;
- Urine Pregnancy test (for women of childbearing potential only);
- The residual study drug in wash-out period will be recoverd, packaged and recorded;
- Whether the subject meets the inclusion/exclusion criteria will be re-evaluated, those meeting the inclusion/exclusion criteria will be randomized to each Ansofaxine dose group or placebo group, and dispensed the study drug. Subjects will receive the study drug on the following day (Day 1);
- The next visit will be scheduled, and the subjects will be remined to bring residual study drug and package back at that visit.

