### Risks and precautions during the study

1. Excerbation of clinical symptoms and suicide

For patients at any age with major depressive disorder, their disease may be possibly exacerbated, regardless of the administration of antidepressants, and they are likely to have suicidal ideation and suicidal behavior as well as abnormal change of behavior, and this risk may continue until the condition is significantly relieve. Depression is known to be associated with some mental disorders and suicide risk, and these mental disorders themselves are the strongest signs of suicide.

For all the subjects receiving the study drug (Ansofaxine Hydrochloride Extended Release Tablet or placebo) for treatment, exacerbation of their clinical symptoms, suicidal tendency and abnormal change in behavior should be closely observed, in particular in the initial stage of drug treatment.

When antidepressants are used for treatment of adult and pediatric patients with major depressive disorder, other psychotic or non-psychotic disorders, the following symptoms may appear: anxiety, agitation, panic attack, insomnia, irritability, hostility, aggression, impulsiveness, restlessness (psychomotor restlessness), hypomania and mania. Although the correlation of the occurrence of the above symptoms with exacerbation of depression and/or suicidal impulse has not been identified, these symptoms may be the foreboding of suicide.

For the subjects with persistent exacerbation of depressive symptoms, suicide or signs associated with it, discontinuation of study drug should be considered, in particular for those whose symptoms are severe, occur suddenly or newly appear.

In this study, the subjects with suicide risk should be excluded.

1. Prolonged QT interval

The in vitro study showed that Ansofaxine Hydrochloride could inhibit the potassium channel coded by hERG, however, no prolonged QT interval was seen overall in the animal study, nor clinically significant prolongation of QT interval was seen in the phase I clinical trial on tolerability. In order to ensure subject’s safety, subjects with clinically significant abnormality on ECG (in particular prolonged QTc interval) should be excluded, and will be monitored through ECG during the study.

1. Blood Pressure

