Appendix 1: Hamilton Depression Scale -17 (HAM-D_17_)

| *Note: 5-grade scoring method with 0～4 points is used for most items. Criteria on each grade: (0) none; (1) mild; (2) moderate; (3) severe; (4) very severe. 3-grade scoring method with 0～2 points is used for few items, the grading criteria are: (0) none; (1) mild to moderate; (2) severe* | | | |
| --- | --- | --- | --- |
| **Item** | | | **Score** |
| 1 | Depressed mood (sad, hopeless, helpless, worthless) | 0=no symptom; 1=narrate only when asked;  2= express spontaneously in conversation;  3= nonverbal expression of this emotion (e.g., through expression, posture, voice and desire to cry);  4= complete expression of this emotion almost by self speech and nonverbal expression | \|_\| |
| 2 | Feeling of guilt | 0=no symptom; 1= blame yourself and feel that you have failed others;  2= Think that you have committed a crime, or think about previous mistakes or misconducts repeatedly;  3= Think of your current illness as a punishment for your own mistakes, or have evil delusion;  4= Hear accusations or condemnations and/or have threatening illusion | \|_\| |
| 3 | Suicide | 0=no symptom; 1=feel pointless in living;  2= Wish I have died or think of something related to death frequently;  3= Negative thought (suicidal thought) or suicide posture  4= Suicidal attempt (any serious attempt will be scored 4) | \|_\| |
| 4 | Trouble falling asleep | 0 = No difficulty in falling asleep;  1= Have a chief complaint of difficulty in falling asleep sometimes (e.g., still unable to fall asleep 30min after going to bed);  2= Have a chief complaint of difficulty in falling asleep every night | \|_\| |
| 5 | Shallow sleeping | 0 = No symptom;  1= Have a chief complaint of shallow sleep at midnight, frequent nightmare;  2 = Wake up at midnight (before 12:00pm) – any case of waking up will be scored 2 (not including  going to the toilet) | \|_\| |
| 6 | Early awakening | 0 = No symptom;  1= Have early awakening, but be able to fall asleep again;  2= Fail to fall asleep again after early awakening | \|_\| |

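### Exclusion 4, read literally, does not exclude a patient rated 3 on the HAM-D17 suicide item for suicidal thought alone, although the protocol says elsewhere that subjects with suicide risk should be excluded

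*Protocol*

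**What the plan says.** Exclusion 4 appears in the same words in the Abstract and in section 5.2: "Subjects who have clear suicide attempt or behavior with Suicide score in HAM-D17 ≥ 3 points".

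Appendix 1 anchors the suicide item of the HAM-D17 from 0 to 4. The anchor at the threshold is "3= Negative thought (suicidal thought) or suicide posture". An attempt scores 4.

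Under safety indicators (section 8.2), the part on risks and precautions states that "In this study, the subjects with suicide risk should be excluded". It gives no score and no definition of suicide risk. For treated subjects it asks that "suicidal tendency and abnormal change in behavior should be closely observed".

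Section 5.3 removes from the trial "Subjects who did not meet the inclusion criteria or met the exclusion criteria".

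**The concern.** The word joining the two halves of exclusion 4 can mean that both are required, or that the score is how the first half is recognised. The anchor for score 3 makes the difference matter, because suicidal thought is neither an attempt nor a behaviour. A site that applies the words as written may randomize such a patient. The chance of allocation to placebo is then 1 in 5, for six weeks, with other antidepressants prohibited under section 6.9. A site that treats the score as decisive turns the same patient away.

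The reading also affects what happens after entry. On the literal reading the patient is eligible. On the other reading the patient met an exclusion criterion and is due for removal under section 5.3. Entry could then also count as a protocol deviation when the per-protocol set is formed.

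**Working it through.** No arithmetic applies. The check sets the criterion against the protocol's own scale anchors and its stated policy.

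**Step 1: the two readings.**
- Literal: excluded if there is an attempt or behaviour **and** a suicide item score of at least 3.
- Score alone: excluded if the suicide item score is at least 3.

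**Step 2: apply both to the Appendix 1 anchors.**

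| Presentation | Item score | Literal reading | Score alone |
| --- | --- | --- | --- |
| Below the threshold | 0 to 2 | Not excluded | Not excluded |
| Suicidal thought, no attempt or behaviour | 3 | **Not excluded** | **Excluded** |
| Suicide posture, taken as behaviour | 3 | Excluded | Excluded |
| Attempt | 4 | Excluded | Excluded |

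The readings part in one row. The table assumes that a posture counts as clear behaviour, which the protocol does not state. If a site did not count it, the posture row would differ as well.

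**Step 3: which reading was intended.** Two features favour the score alone. The first is the policy statement on suicide risk in section 8.2. The second is the threshold itself: a serious attempt already scores 4, so a cut at 3 does little if an attempt or behaviour is required anyway.

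**Step 4: does other text close the gap?**
- The Abstract repeats the same sentence, so it cannot settle the reading.
- Exclusion 9 (investigator judges that ECT is needed now) and exclusion 18 (investigator judges the subject unsuitable) are discretionary.
- Close observation under section 8.2, and withdrawal under section 5.4 for suicide during the study or on the investigator's judgement, act after entry.
- At baseline, "Whether the subject meets the inclusion/exclusion criteria will be re-evaluated", but this applies the same sentence a second time.
- Among the scales scheduled in the flow chart, only the HAM-D17 has a suicide item, so no other scheduled rating would catch the patient.

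None of these makes a score of 3 for thought alone a listed ground for exclusion.

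**The case against.** The strongest reply is that the intended meaning is plain. The policy statement is an instruction about who should be excluded, it is not worded as optional, and exclusion 4 supplies the score that it lacks. A site would have to read the criterion narrowly and ignore the policy to randomize this patient, and nothing in the protocol shows that any site would. Much of this stands. Intent does favour the wider reading, and divergence between sites is a possibility rather than a documented fact. It does not remove the defect: sites check subjects against the listed criteria, and the listed criterion, followed to the letter, admits a patient whom the policy says to exclude.

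Three stronger conclusions might be inferred, and the documents do not support them.

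- **That the missing visit is a defect in itself.** A neighbouring criterion does name its visits: "Subjects who have Depressed Mood of Hamilton Depression Scale (HAM-D_17_) ≥2 points at the screening and baseline visit". But the flow chart schedules both the HAM-D17 and the eligibility check at Visits 1 and 2. Sections 7.1 and 7.2 apply the exclusion criteria before wash-out and again before randomization. The score therefore applies at both visits already.
- **That exclusion 4 is the only entry rule that mentions suicide.** The policy statement in section 8.2 is also a direction on entry. What it lacks is a score or definition.
- **That rewording would stop a remote past attempt from excluding a patient.** Both readings already require a score of at least 3, so a past attempt with a lower present score excludes nobody now.

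**Conclusion.** The point holds as a safety-relevant fault of wording. The literal text of exclusion 4 falls short of the protocol's own stated policy for one group: suicide item score 3 for suicidal thought, without attempt or behaviour. How many screened patients this would be cannot be estimated, because the protocol gives no distribution of the item.

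The conclusion rests on the Appendix 1 anchor as written and on sites working from the listed criteria. It does not imply that the sponsor meant to admit patients with suicidal thought rated 3; the evidence on intent points the other way. It has no bearing on the primary analysis, the sample size or the type I error.

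**What to change.** In the Abstract and in section 5.2, replace item 4 by:

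*Subjects with a HAM-D17 Suicide item score ≥3 (suicidal thought, suicide posture or attempt) at screening or baseline.*

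Change the eligibility checklist to match. Naming the visits only writes down what the schedule already implies.

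The change is one sentence in two places plus the checklist. It uses a rating that is already made at both visits and adds no assessment. The downside is some additional screen failures, namely patients scoring 3 for thought alone at any site that reads the present rule literally. Their number cannot be estimated from the protocol.

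Whether a past attempt with a present score below 3 should also exclude is a separate clinical choice for the sponsor. Neither reading of the current text covers that group, so adding it would change eligibility rather than clarify it.
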